The **primary endpoint** will focus on preliminary analysis of the wearable sensor data. We will assess the relationship between wearable sensor parameters (such as heart rate variability, physical activity, and posture) and self-reported pain intensity in participants with chronic visceral pain. We aim to determine whether specific physiological markers—such as body posture— can reliably predict or associate with pain levels. This analysis will provide clinically useful insights into how wearable sensor data can be used to quantify and monitor visceral pain in real-time.

The **secondary endpoints** will focus on exploratory analyses, including:

Pinpointing the functional pathways involved in the development and progression of chronic visceral pain through genetic analysis. This will help us understand why some individuals develop severe pain while others do not, even with similar disease activity.Identifying genetic variants that may regulate visceral pain, particularly in individuals whose pain severity does not align with the activity of their disease. This analysis will explore both known and novel genetic factors that contribute to pain perception.Investigating the presence and concentration of autoantibodies to explore their potential role in chronic visceral pain and immune-mediated mechanisms that may contribute to pain persistence.Identifying distinct clinical phenotypes of visceral pain using clustering techniques to group participants by shared characteristics, such as disease type, pain severity, and wearable sensor data. These clusters will be analysed for potential genetic or immune-related differences.Exploring pain frequency, location (using body maps), and time-series data from self-reported pain ratings to uncover patterns that can help characterize visceral pain flares.

By studying these diverse participant groups and collecting detailed physiological, genetic, and self-reported data, this research aims to provide new insights that could lead to improved diagnostics, treatments, and future studies on chronic visceral pain.

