### Primary endpoint analysis

The primary hypothesis we will test is that specific physiological parameters measured by wearable sensors (such as heart rate, physical activity, or respiration) will associate with self-reported pain intensity and specific body postures, such as sitting or lying down. We hypothesize that:

Higher pain scores will associate with reduced mobility and specific postures (e.g., sitting or lying down).Wearable sensor data will provide objective measures that can predict or associate with self-reported pain intensity.

This hypothesis will be tested using a linear multiple regression model with the following four predictors:

1Heart Rate Variability2Physical Activity (as measured by accelerometery)3Posture (sitting, standing, lying down)4Mean daily respiration rate

We expect that a sample size of n = 100 exclusively for the wearable sub-study provides 80% power to detect a moderate effect size (f² = 0.12 or larger) at p < 0.05, assuming four predictors.

For the primary analysis, we will fit a multiple linear regression model with mean daily visceral pain intensity as the dependent variable and the four pre-specified wearable predictors as independent variables. Model diagnostics will include inspection of residual-versus-fitted plots, Q–Q plots, and tests to assess both normality of residuals and multicollinearity between predictors. If substantial non-linearity or heteroscedasticity is detected, we will explore appropriate transformations of predictors or outcome while retaining the same pre-specified predictor set. All analyses will be conducted using validated statistical packages (either in R or Python), and the final model specification, diagnostics, and code will be documented to support reproducibility.

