These four predictors were selected *a priori* based on established physiological relationships with pain states. Heart rate variability reflects autonomic nervous system engagement known to correlate with pain perception and flare severity in visceral pain syndromes [33–35]. Physical activity reduction is an established behavioural marker of pain avoidance and flare severity [36–38]. Posture is critical in visceral pain as many patients adopt characteristic positions during flares (e.g., lying down during endometriosis flares) [39,40]. Respiration rate was selected over alternative markers (such as skin temperature or sleep metrics) because: (i) it is directly modulated by nociceptive signalling through brainstem-vagal pathways critical to visceral pain processing [41,42], (ii) respiratory patterns are objectively measured with high fidelity by our chest-worn sensors, (iii) respiration is feasible for continuous long-term monitoring without imposing additional participant burden. Skin temperature was not selected due to confounding by environmental factors, and sleep metrics, whilst potentially informative, require longer data epochs incompatible with our primary real-time flare detection objective. No additional predictors will be included in this primary model.

We will use the correlation coefficients and regression analyses described to evaluate associations between these parameters and self-reported pain intensity, measured on an 11-point Likert scale (0–10). Confounding variables such as age, diagnosis, and occupation will not be included in the primary model but will be explored in sensitivity analyses.

Where multiple days of valid wearable data are available per participant, we will first derive participant-level mean values for each predictor over the observation period and use these aggregated values in the primary regression model; this avoids inflating the effective sample size and simplifies interpretation at the participant level. Day-level models will also be explored by using linear mixed-effects models with a random intercept for participant data.

Given that not all participants from the Extreme Pain cohort will use the wearables, the total number of participants we aim to recruit in the Extreme Pain cohort needs to exceed 100 to ensure adequate statistical power for this primary hypothesis. Healthy controls are not included in this confirmatory analysis, as they are unlikely to report sufficient pain scores for reliable modelling.

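### The protocol does not fix which test decides its only confirmatory claim: the powered test is global, the claim is about specific markers, and correlations are offered as a second route

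*Protocol article*

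**What the plan says.** The protocol describes the deciding analysis in several ways.

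- **Abstract:** the primary confirmatory outcome is presented as a correlation between sensor parameters and self-reported pain.
- **Aims and endpoints:** the primary endpoint is about individual markers: "We aim to determine whether specific physiological markers", with body posture as the example, predict or associate with pain. The same section promises a pre-specified model for the confirmatory part.
- **Primary endpoint analysis, hypothesis:** "specific physiological parameters measured by wearable sensors (such as heart rate, physical activity, or respiration) will associate with self-reported pain intensity". A sub-hypothesis names reduced mobility and particular postures.
- **Primary endpoint analysis, test:** "This hypothesis will be tested using a linear multiple regression model with the following four predictors" (heart rate variability, physical activity, posture, respiration rate). Participant-level means are used and no further predictors are allowed.
- **Primary endpoint analysis, power:** "a sample size of n = 100 exclusively for the wearable sub-study provides 80% power", for f² = 0.12 or larger, "at p < 0.05, assuming four predictors". This is the only significance level given for the primary analysis.
- **Primary endpoint analysis, evaluation:** "We will use the correlation coefficients and regression analyses described to evaluate associations between these parameters and self-reported pain intensity". The number, type and role of the correlations are not given.

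Multiplicity corrections are stated only for the exploratory SNP analysis (Key exploratory endpoint).

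**The concern.** Three different results could be reported as the primary finding: a significant overall model, a significant adjusted coefficient, or a significant pairwise correlation. They answer different questions. The overall F test says only that at least one predictor is related to pain. A coefficient concerns one marker given the other three. A correlation concerns one marker without adjustment. When the predictors are correlated, which the plan anticipates by checking multicollinearity, a coefficient and a correlation for the same marker can disagree.

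The wording of the hypothesis and endpoint invites a claim about a named marker, while the sample size appears to be set for the overall test. At stake is whether the stated 5% level applies to the sentence that will appear as the primary result.

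**Working it through.** **Inputs from Primary endpoint analysis:** n = 100, f² = 0.12, alpha 0.05, four predictors, stated power 80%, one row per participant.

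**Assumed, because the protocol gives no figure:** a common pairwise correlation ρ between predictors of 0 to 0.7; normal data; under the null, pain unrelated to every predictor.

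**Step 1. Which test does the power statement describe?** The noncentrality is λ = f² × n = 0.12 × 100 = 12.

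| Test at n = 100 | Power | n for 80% |
|---|---|---|
| Overall test, 4 df, large-sample chi-square | 80.2% | 11.94 / 0.12 = 99.5, so 100 |
| Overall F test, 4 and 95 df, exact | 78.0% | 105 |
| One coefficient at 0.05 | 92.9% | 68 |
| One Pearson correlation at 0.05, r = √(0.12/1.12) = 0.327 | 91.7% | not computed |
| One coefficient at 0.05/4 = 0.0125 | 81.8% | 97 |

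At the stated level of 0.05, only the overall 4-df test comes close to the stated 80%. The large-sample form reproduces n = 100, and the exact F is two points lower. A Bonferroni-adjusted coefficient also comes close, but at a level the protocol does not mention.

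**Step 2. False-positive rate under each decision rule.** For four independent tests at 0.05, 1 − 0.95⁴ = 18.5%. Null simulation with n = 100, four predictors and 30,000 runs per setting:

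| ρ | Any coefficient | Any coefficient or correlation | Overall F only | F significant, then any coefficient |
|---|---|---|---|---|
| 0 | 17.6% | 20.0% | 4.8% | 4.7% |
| 0.2 | 17.8% | 22.2% | 4.6% | 4.4% |
| 0.3 | 17.8% | 23.5% | 4.8% | 4.5% |
| 0.5 | 17.4% | 24.8% | 5.0% | 4.4% |
| 0.7 | 16.9% | 24.7% | 4.9% | 4.2% |

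A smaller simulation (6,000 runs per setting, ρ of 0, 0.3 and 0.5) gave 16.1–18.0% for any coefficient and 20.5–23.6% for either route.

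**Step 3. Sensitivity to posture coding.** Posture lists three categories but is counted as one predictor. Entered as two terms, it gives 20.8–22.2% for any coefficient and 25.6–29.5% for either route. The overall F test stays at about 5%, but its exact power falls to 74.0%.

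**Step 4. Why a gate alone is not enough.** The last column of the Step 2 table holds when no predictor matters. If one marker is truly related to pain, the F test will usually be significant. The other three coefficients, read at 0.05, then carry up to about 1 − 0.95³ = 14.3% (independent tests) for at least one false marker claim. Hence the adjustment after the gate.

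**The case against.** The strongest reply is that the protocol does specify one model: one outcome, four named predictors, no additions, one row per participant, confounder adjustment left to sensitivity analyses and day-level models labelled as explored. The power statement fits the overall test of that model, and on that reading the error rate is 5%. No sentence says that each coefficient and each correlation is tested at 0.05, or that any one significant result confirms the hypothesis. The article is also condensed, and an analysis plan not shown here may name the deciding statistic.

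Most of this stands. A reader might infer that the protocol has no single primary analysis, or that its false-positive rate is 16–25% rather than 5%. The document supports neither: a single regression is pre-specified, and p < 0.05 appears for the primary analysis only in the power sentence.

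The reply does not remove the conflict inside the article. The abstract names a correlation, the test sentence a regression, and the evaluation sentence both. The claim is about specific markers while the powered test is global. The article presents this analysis as already pre-specified and as aligned with SPIRIT on primary hypothesis tests. A separate analysis plan could settle the rule, but these statements would still need reconciling.

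**Conclusion.** The concern holds as an unresolved decision rule, not as a demonstrated inflation. The power figure points to the overall 4-df test, which keeps the error rate at 5% but cannot on its own support the marker-specific, partly directional claims in the hypothesis and endpoint. If those claims are made from unadjusted coefficients, the false-positive rate is about 16–18%; if correlations count as well, it is about 20–25%. Both ranges depend on an any-result-counts rule that the protocol neither states nor excludes, on four model terms, and on assumed predictor correlations of 0 to 0.7. The point should be settled because this is the study's only confirmatory test and, according to Study status, no analysis has yet been done.

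**What to change.** - Name the overall F test of the four-predictor model at 0.05 as the single primary test, in line with the power statement.
- Make claims about individual markers only if that test is significant, using Holm-adjusted tests of the coefficients.
- Report the pairwise correlations descriptively with confidence intervals and no confirmatory claim.
- Reword the abstract so that the confirmatory outcome is the regression.

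This takes a few sentences and no new data. The cost is power for single markers. At Holm's strictest step (0.0125), one coefficient with partial f² = 0.12 has 81.8% power, against 92.9% at 0.05. If that marker carries the whole effect, power after the gate cannot exceed the 78.0% of the exact F test itself.

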**Fig 3 pone.0350169.g003:**
[figure not shown]
Wearable Sensor Deployment and Participant Instructions for the ADVANTAGE Study. Chest-worn respiratory sensor and wrist-worn physiological monitor setup for 4-week continuous data collection from Extreme Visceral Pain and Healthy Controls cohorts. Diagram illustrates wireless charging station, 2-metre Discovery App tablet sync range for data upload, daily reapplication protocol (shower before reattachment, correct orientation), and smartphone app for *ad libitum* pain reporting (0-10 Likert scale). Key operational constraints shown: non-waterproof (daily removal for showering), medical imaging contraindication (X-ray/MRI interference), QR code access to instructional videos. Ensures compliance for primary endpoint analysis correlating respiration rate, HRV, activity, and posture against real-time pain scores.

**Upper limb *smartwatch*:** The wrist-worn device (ActiGraph GT9X Link or GENEActiv, for Cambridge and Edinburgh sites, respectively) records limb movement and position continuously for up to 90 days. Data is downloaded after the wearable is returned, either by post or during a follow-up visit.

***ADVANTAGE Diary* remote mobile app questions during wearable sub-study:** Pain severity will continue to be recorded through the *ADVANTAGE Diary* app using the same 11-point scale as with the cohort classification stage. Participants will also receive daily reminders, and those who report pain will be asked additional questions: “How worried are you about that pain?” (rated 0–10), and “What is the position of your body right now?” (options include sitting, standing, lying down, squatting, moving actively). Those using the smartwatch and the *ADVANTAGE Diary* remote mobile app will be invited to continue for up to 90 days or until the smartwatch battery runs out after the follow up visit.

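### The primary model takes a participant mean of posture, a three-category variable counted as one of four terms; the averaged code is arbitrary, and the sensible time-share reading needs a fifth term that the power statement does not cover

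*Protocol article*

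**What the plan says.** All of this is in the Primary endpoint analysis section of the protocol article unless noted.

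- The model is a "multiple linear regression model with mean daily visceral pain intensity as the dependent variable and the four pre-specified wearable predictors as independent variables". The four are heart rate variability, physical activity, posture and mean daily respiration rate. Posture is described only by its three categories.
- The set is closed: "No additional predictors will be included in this primary model".
- Where a participant has several valid days, "we will first derive participant-level mean values for each predictor over the observation period and use these aggregated values in the primary regression model". Posture is not excepted, and no numeric code, time share or continuous posture score is given.
- The directional hypothesis is "Higher pain scores will associate with reduced mobility and specific postures (e.g., sitting or lying down").
- On sample size, "a sample size of n = 100 exclusively for the wearable sub-study provides 80% power" for a "moderate effect size (f² = 0.12 or larger) at p < 0.05, assuming four predictors".
- Day-level mixed models are to be explored; they do not replace the participant-level model.

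**The concern.** Three of the predictors are numeric and can be averaged over days. Posture, as defined, cannot: its categories have no order and no numbers, so a single mean exists only after someone chooses a numbering, and the result depends on that choice. The hypothesis groups sitting with lying. A numbering that puts standing between them places the two hypothesised postures at opposite ends of the scale.

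The natural repair is to average category indicators, which gives the share of time in each posture. Three shares sum to one, so two are free. Posture then takes two terms, and the model has five rather than four.

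This is the study's one confirmatory test, and posture is named in its hypothesis. If the derivation stays open, the coding can be chosen after the data are seen. The Study status section says that no analysis has yet been done, so it can still be settled cleanly.

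**Working it through.** **1. The plan's own power figure.** Inputs from the article: n = 100, f² = 0.12, α = 0.05, four predictors. Test of the whole model with u terms: noncentrality λ = n·f² = 100 × 0.12 = 12; denominator df v = n − u − 1.

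- Large-sample chi-square, 4 df, λ = 12: power 80.2%. This reproduces the stated 80%.
- Exact noncentral F, u = 4, v = 95, λ = 12: power 78.0%. The f² detectable with 80% power is 0.125, and f² = 0.12 would need n = 105.

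The stated figure is therefore a four-term figure, with one term for posture.

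**2. The same with posture as two shares.** u = 5, v = 94, λ = 12:

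| | 4 terms | 5 terms |
|---|---|---|
| Chi-square power | 80.2% | 76.9% |
| Exact F power | 78.0% | 74.0% |
| n for 80% power (exact) | 105 | 113 |
| f² detectable at n = 100, 80% power (exact) | 0.125 | 0.136 |

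This holds f² at 0.12 and so assumes that splitting posture adds no explained variance.

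**3. What a mean code does.** Number the categories in the listed order: sitting 1, standing 2, lying 3. This numbering is an assumption. With shares S, T, L summing to 1, the mean is S + 2T + 3L = 2 − S + L. A participant at 40% sitting, 20% standing, 40% lying scores 2 − 0.4 + 0.4 = 2.0. One at 10%, 80%, 10% scores 2 − 0.1 + 0.1 = 2.0. The hypothesis expects different pain in these two.

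**4. Size under assumed inputs.** Suppose a 1-SD rise in pain moves a points of time to sitting and b points to lying, with independent residual SDs of 10 and 5 points. The mean code then moves with b − a and the combined sitting-or-lying share with a + b. Both have residual variance 10² + 5² = 125.

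| a, b | r, mean code | r, combined share |
|---|---|---|
| 2, 2 | 0/√125 = 0.00 | 4/√(16 + 125) = 0.34 |
| 3, 1.5 | −1.5/√(2.25 + 125) = −0.13 | 4.5/√(20.25 + 125) = 0.37 |
| 0, 4 | 4/√(16 + 125) = 0.34 | 0.34 |

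At n = 100 in posture-only models, simulated power for the mean code is about 5.5% in the first row, 25% in the second and 94% when only lying shifts.

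A second simulation used Dirichlet(4, 3, 4) shares for sitting, standing and lying, equal effects of 2.5 for sitting and lying, and residual SD 1. The listed-order code rejected in 5.3% of runs. Two numberings with standing at one end rejected in 74% and 75%, and the joint test of two shares in 81%.

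**The case against.** The article never assigns numbers to posture. Averaging over days can fairly be read as averaging daily values, and if the daily value is a time share its mean is valid. How a sensor variable is derived is often left to a fuller document. This stands as far as it goes: a sensible reading exists, and the 1/2/3 code is only an illustration. But the article does more than stay silent. It fixes the mean for every predictor, the count of four, the closed set and the power for four. A fuller document could adopt two shares only by departing from the count, or one share only by choosing which.

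Three stronger conclusions may tempt a reader, and the documents support none of them.

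- *That the averaged code will cancel the posture effect.* Full cancellation needs standing numbered midway and equal shifts to sitting and lying. The hypothesis offers those two postures as examples and does not name standing as the contrast. If mainly lying shifts, the listed-order code keeps the effect.
- *That the association is unstable in sign.* Numbering standing highest or lowest reverses the scale. Both orders say that more pain goes with less standing, and both keep most of the power.
- *That the diary's posture item must be mapped to the model.* It has five choices ("options include sitting, standing, lying down, squatting, moving actively"), but nothing says it supplies the posture term. The model's predictors are called wearable predictors, Aims and endpoints says that sensors track posture, and the Fig 3 caption lists posture among the measures for the primary analysis.

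The simulations are also posture-only, so they do not measure the effect on the four-predictor test.

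**Conclusion.** The point holds as a conflict among stated rules. A participant mean of an unordered three-level category has no fixed meaning, and the reading that gives it one needs a term that the predictor count and power statement do not allow for. The firm number is the power cost of the two-share reading: from 78.0% to 74.0% by exact F at n = 100 and f² = 0.12, or a detectable f² of 0.136 instead of 0.125. It rests only on the article's inputs and a fixed f². The loss from an averaged code ranges from complete to none, depending on the numbering and on which postures shift with pain; the documents supply neither.

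**What to change.** In Primary endpoint analysis, except posture from the mean rule and define it in one sentence: the participant-level posture value is the proportion of valid wearable time spent sitting or lying down, entered as a single term. This keeps four terms, the closed predictor set and the present basis for power, and it matches the hypothesis. It needs no new data. Its cost is that sitting and lying are not separated, so it is less sensitive if only one of them moves. With the residual SDs assumed above and a shift of 2 points to lying alone, the combined share correlates with pain at 2/√(4 + 125) = 0.18 and the lying share at 2/√(4 + 25) = 0.37.

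If that distinction matters, enter the sitting share and the lying share with standing as reference, and test them jointly on 2 df. State that the model has five terms and restate the power: about 74% at n = 100 and f² = 0.12, or 80% for f² of about 0.136. Either choice should be recorded before any data are analysed.

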### Aims and endpoints

The overarching aim of this study is to deepen our understanding of chronic visceral pain by identifying and evaluating the genetic, molecular, and physiological mechanisms that contribute to this condition. We will examine these mechanisms across different participant groups, including those with extreme visceral pain, those with a lack of expected pain despite visceral disease, and healthy controls.

Our **primary objective** is to look for physiological markers (such as changes in movement, heart rate, and postural patterns) that predict or associate with visceral pain flares by examining data from wearable sensors. This will provide objective, real-time insights into how visceral pain affects day-to-day activities, and will be tested using a pre-specified statistical model and is central to the confirmatory aspect of the study.

In addition, we will undertake a series of **secondary/exploratory objectives**, which include the following key areas of investigation:

1**Genetic insights:** We aim to identify and characterize the genetic factors that underlie chronic visceral pain in specific participant cohorts, which include individuals with conditions like polycystic kidney disease, inflammatory bowel disease, chronic pancreatitis, endometriosis, and painful bladder syndrome.2**Spatial and temporal pain mapping:** We will create detailed maps of where and when individuals experience visceral pain. This includes analysing the frequency and intensity of pain reported by participants using a remote mobile app and wearable sensors that track body movement, posture, heart rate, and breathing.3**Biological sample analysis:** We will collect a variety of biological samples—blood, urine, low vaginal swabs, and faeces—from participants to explore pain mediators and modulators. This will include testing human serum in passive transfer experiments using mice to better understand the role of autoantibodies and other pain-related factors [19].4**Comparing pain groups:** We will compare participants with high levels of visceral pain, regardless of disease activity, to those with little or no visceral pain despite having active disease. These groups will be contrasted with healthy control subjects to uncover key differences in pain experience and physiology.

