### Wearable sensors

Participants from Extreme Visceral Pain and Healthy Controls cohorts will use two types of wearable sensors to monitor physiological data:

**Chest *wearable sensor*:** The Discovery *ANNE* Chest System is a flexible, rechargeable sensor worn on the upper chest for up to 16 hours daily over 30 days. It tracks heart rate, respiratory rate, skin temperature, and activity level. Participants will answer two questions daily via a mobile app in a tablet linked to the sensor: “Have you had a visceral pain flare today?” and “Have you changed or cancelled an activity due to visceral pain today?”. To encourage adherence to the wearable sensor usage protocol, instructional videos on how to wear the devices were made publicly available and shared with participants (see Supplementary Information). Additionally, Fig 3 is printed and shared with the participants to provide a visual guide with key steps for sensor setup, syncing, and daily use.

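### The primary objective concerns pain flares in real time, but the confirmatory regression on participant means tests only a between-person association with average pain intensity

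*Protocol article*

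**What the plan says.** **Objective.** Under Aims and endpoints, the primary objective is to find sensor markers "that predict or associate with visceral pain flares by examining data from wearable sensors". The same paragraph says that this "will be tested using a pre-specified statistical model and is central to the confirmatory aspect of the study". Under Primary endpoint analysis, sleep metrics are turned down because they "require longer data epochs incompatible with our primary real-time flare detection objective", and activity and posture are justified partly by how patients behave during flares.

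**Endpoint and hypothesis.** The primary endpoint (Aims and endpoints) and the hypothesis (Primary endpoint analysis) are worded differently. Both concern the relation of sensor parameters to self-reported pain intensity. Neither makes flares the outcome.

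**Model.** The primary analysis is a multiple linear regression of mean daily pain intensity on heart rate variability, activity, posture and respiration rate. Where a participant has several valid days, "we will first derive participant-level mean values for each predictor over the observation period and use these aggregated values in the primary regression model". The reasons given are to avoid inflating the effective sample size and to ease interpretation at participant level. The averaging is stated for the predictors. A single outcome value per participant is implied by that reasoning and by the power basis of n = 100. Other day-level work is secondary: "Day-level models will also be explored by using linear mixed-effects models with a random intercept for participant data".

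**Flare data.** Wearable sensors describes a daily question, "Have you had a visceral pain flare today". It does not enter the primary model.

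**The concern.** A flare is an event within a person over time. To learn whether a marker accompanies or precedes flares, one compares a person's worse days with the same person's better days. The confirmatory model has no flare variable and no time dimension, and it compares people with one another. The two associations can differ in size and even in sign.

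The only confirmatory test could therefore miss a marker that tracks pain in every participant. It could also be significant because, for example, less active people have higher average pain, and then be reported under the stated objective as a marker of flares. The second error is the more likely to mislead, because the article promises real-time monitoring.

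**Working it through.** **1. The plan's own figure.** Inputs from Primary endpoint analysis: n = 100, four predictors, f² = 0.12, alpha 0.05, stated power 80%. For the overall F test with 4 and 95 degrees of freedom and λ = f² × n = 0.12 × 100 = 12, power is 78.0%. This is 2 points short; 80% needs n = 105, or f² of about 0.125. The shortfall is minor and is not the point here. What matters is that the calculation counts 100 participants as the independent units, so the powered test is between-person.

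**2. What the participant-mean slope estimates.** Write the predictor for person i on day t as X = mᵢ + dᵢₜ, and pain as β_B·mᵢ + β_W·dᵢₜ + aᵢ + eᵢₜ. With T days and equal between-person and daily predictor variance (assumed), the slope on participant means tends to

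(β_B + β_W/T) / (1 + 1/T).

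At T = 28:
- β_W = 0.3, β_B = 0: (0.3/28)/(1 + 1/28) = 0.0103. The within-person effect almost vanishes.
- β_W = 0, β_B = 0.5: 0.5/(1 + 1/28) = 0.483 (simulated 0.480).
- β_W = +0.3, β_B = −0.5: (−0.5 + 0.0107)/1.0357 = −0.472 (simulated −0.471). The sign is opposite to the within-person effect.

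**3. Rejection rates.** The documents give no day-level variances or slopes, so all sizes here are assumed.

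*Set A:* 100 participants, 28 days, four predictors with SD 1 at each level and the same slope for each, person-intercept and residual SD 1.5.

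| True association | Participant-mean F test | Within-person day-level test |
|---|---|---|
| Within only, slope 0.15 | about 5% | 100% |
| Between only, slope 0.25 | 68% to 71% | 3.5% to 6% |
| Same slope at both levels, 0.15 | 28% to 30% | 100% |
| Same slope at both levels, 0.25 | 73% to 74% | 100% |
| Same slope at both levels, 0.30 | 88% to 90% | 100% |

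Ranges are across repeated simulation runs. Analytic check of the shared-slope rows: f² ≈ 4 × slope² / 1.5², so 0.15 gives 0.09/2.25 = 0.04, λ = 4, power 31%; 0.30 gives 0.36/2.25 = 0.16, λ = 16, power 90%.

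*Set B:* 14 or 28 days, one active predictor with within-person slope 0.1 to 0.5, no between-person slope, residual SD 1, person-intercept SD 0.5 to 2. The participant-mean test rejects in about 4% to 7% of runs; the within-person test rejects in 82% to 100%.

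**The case against.** The strongest reply is that the hypothesis and endpoint concern pain intensity, and a participant-level regression can test both as written. This stands. A reader might infer that the confirmatory analysis answers nothing the trial asks; the documents do not support that. On the same reading, the 68% to 71% rejection in the between-only case is correct detection of a person-level association. It becomes misleading only if reported as evidence about flares.

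Second, the 5% figure follows from setting the between-person slope to zero. This also stands: it is a limiting case, and the table shows higher power when the two slopes agree.

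Third, averaging need not erase all information on flares, since frequent flares raise a person's mean pain and shift mean sensor values. That is fair. However, when flares were simulated as the only link, with flare rates varying between people and assumed sizes, the participant-mean test rejected in only 6% to 24% of runs.

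Fourth, aggregation is a disclosed choice made to avoid inflating the sample size. The aim is sound, but a mixed model or participant-clustered standard errors meets it without discarding within-person information.

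Two further inferences should not be drawn:
- That sensor and diary means may cover different windows, 30 against 90 days. The article describes the longer period as an invited continuation after the follow-up visit, and its Fig 3 caption ties four weeks of collection to the primary analysis.
- That the exploratory mixed model is faulty for lacking person-centring. A full analysis plan may settle that.

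None of this removes the mismatch. The article itself designates the flare objective as confirmatory and fixes the unit of analysis.

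**Conclusion.** The concern holds as a mismatch between the stated primary objective and the confirmatory model. The model tests a between-person association with average pain intensity. It cannot show whether markers move with pain or flares within a person, so neither a positive nor a null result settles the flare objective.

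If the association is purely within-person, the planned test rejects at about its 5% type I error. If a between-person association of the same sign exists, its power is higher but, in the cases run, still below that of a within-person test. The percentages rest on assumed slopes, variances and 14 or 28 valid days. The distinction between the two questions does not depend on those values.

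**What to change.** Make the day-level mixed model, which the article already plans, the confirmatory analysis:
- Outcome: pain on that day, using days with both a pain rating and sensor data.
- Predictors: the same four, each entered as the participant's mean and as that day's deviation from it.
- Test: a joint test of the deviation terms, with a participant random intercept and either random slopes or participant-clustered standard errors.
- Power: restated for this test.
- Supporting analyses: keep the participant-mean regression as supportive, and use the daily flare question as a secondary outcome.

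The daily ratings, sensor data and flare question are already collected, and Study status says that no analysis has been performed, so the change can still be pre-specified. The costs are that the between-person association becomes supportive, and that the new power figure needs assumed day-level variances and diary completion, which the article does not give. Whether 100 participants suffice should be shown under those assumptions.

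At minimum, if the participant-mean model stays confirmatory, restate the primary objective and its conclusion as a between-person association with average pain intensity, with no claim about flares or real-time detection. That costs only wording.
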